### Consensus and stability

Consensus for this Delphi study will be defined as ≥75% agreement (or disagreement) on the Likert scale, and for option(s) in multiple-choice statements. Stability of the responses will be calculated through non-parametric χ^2^ tests for multiple–choice statements and Kruskal-Wallis tests for Likert scale statements from round 2 onwards. A p value <0.05 will represent significant variation in the responses, and the statement will be repeated in the subsequent Delphi round. Open-ended responses from participants will be analysed using thematic analysis to identify recurring ideas and insights. Two independent researchers will code the data, with discrepancies resolved by discussion or a third reviewer. Open–text comments to survey questions will inform revisions to the questions for the subsequent Delphi rounds. Where more than 10% of responses include congruent comments on a particular item, the item will be modified for subsequent Delphi rounds.

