**Methods:**

A Delphi consensus process will be conducted, engaging an international multidisciplinary group of 30–40 panellists, including clinicians, researchers, patients, public representatives and health economists. Through iterative rounds, the study will seek agreement on the individual components of the PPCs composite. Additionally, consensus will establish a framework for a composite outcome measure based on a standardised severity classification, appropriate timeframes and weighted grading of PPCs.

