**Analysis:**

Consensus, defined by ≥75% concurrence in multiple choice questions or on Likert–scale statements, will be evaluated from round 2 onwards. Delphi rounds will be continued until all statements have reached stability of responses evaluated by χ^2^ tests or the Kruskal-Wallis test.

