### Panellists

An international panel of 35–40 panellists from six continents, including patient representatives, will be invited to this Delphi study. A concerted effort will be made to include panellists from LMICs, as well as for an age and sex balance.

Panellists will be identified based on *either of* the following criteria:

At least 10 years of clinical experience as a staff member in Anaesthesiology, Surgery or Intensive Care Medicine with involvement in care of patients with postoperative complications.Author of at least three publications (observational studies or randomised clinical trials) using PPCs as a primary or secondary outcome.

The predefined selection criteria will facilitate a balanced composition of panellists possessing clinical or academic expertise in the field of PPCs. This approach will enhance the relevance, reliability and generalisability of the consensus findings. Panellists will be identified through a purposive sampling from the publications on PPCs and meeting the above–mentioned selection criteria. On confirming their acceptance, the panellists will be provided with a succinct summary of the Delphi process, explaining the role and objectives, expected schedule of Delphi surveys and duration required to complete each survey. To encourage continuing engagement of the panellists and to help prevent them from dropping out before completion of the full process, at least three personalised email reminders will be sent during each Delphi round, in addition to an effort to establish personal contact. Furthermore, all panellists will be recognised as collaborative authors in the final publication in appreciation of their professional expertise. Should the attrition rate of panellists exceed 20%, a sensitivity analysis will be conducted with the plausible worst–case and best–case scenarios, considering the opinion of non-responders.

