### Delphi rounds

Panellists and their responses will remain anonymised during the Delphi Rounds. Search results will inform the opening statements of the Delphi Rounds. The statements will be prepared on Google Forms as multiple–choice or 7-point Likert scales. Delphi round surveys will be presented to panellists through a unique online link. Multiple iterative Delphi rounds will be conducted until stable responses are achieved for all statements. Delphi round reports and patient–centred outcomes obtained from the interviews and questionnaire, as well as anonymised cumulative feedback, will be shared with panellists (figure 1).

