### Consensus process

This study adopts a mixed-methods consensus design to ensure comprehensive stakeholder involvement. Two parallel methodologies will be employed:

Nominal group technique (NGT): to gather and prioritise perspectives from patients and patient care representatives, a structured NGT approach will be used. This technique facilitates in–depth discussion and the ranking of PPCsin a virtually moderated setting. It ensures that diverse lived experiences are reflected and incorporated into the prioritisation process.

Modified Delphi methodology: for consensus among panellists, a modified Delphi process will be undertaken. This will involve multiple anonymous iterative survey rounds, enabling participants to rate and revise their responses based on group feedback.

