### Final consensus

The stable statements from Delphi rounds will inform the consensus definition, components, timeframe and appropriate monitoring of PPCs and will be vetted by panellists before publishing.

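### A non-significant independent-samples test is read as proof of stability in paired Delphi responses, so small and moderate shifts near the 75% line will usually be called stable

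*Protocol article*

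**What the plan says.** Under Consensus and stability, the protocol article assigns chi-square tests to multiple-choice statements and "Kruskal-Wallis tests for Likert scale statements from round 2 onwards". The decision rule follows: "A p value <0.05 will represent significant variation in the responses, and the statement will be repeated in the subsequent Delphi round".

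The result of this test ends the study. The abstract states that "Delphi rounds will be continued until all statements have reached stability of responses", and the Delphi rounds section repeats it: "Multiple iterative Delphi rounds will be conducted until stable responses are achieved for all statements". Under Final consensus, "The stable statements from Delphi rounds will inform the consensus definition, components, timeframe and appropriate monitoring of PPCs".

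The Consensus process section describes anonymous iterative rounds "enabling participants to rate and revise their responses based on group feedback", so the same people answer successive rounds. The panel size is "engaging an international multidisciplinary group of 30–40 panellists" in the abstract and "An international panel of 35–40 panellists from six continents" in the Panellists section. This difference does not affect the point.

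The article does not say which samples the tests compare. A comparison between rounds is the natural reading of stability. No permitted amount of change, agreement statistic or detectable shift is given. The coefficient-of-variation rule applies only to the weightage rounds.

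**The concern.** Two features of the stated rule work together.

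- **Data structure.** Chi-square and Kruskal-Wallis tests assume independent groups. When the same panellists answer twice and their answers are positively correlated, these tests overstate the variance of the between-round change. They then reject too rarely.
- **Direction of inference.** Only p<0.05 sends a statement to another round. By implication p≥0.05 means stable, although the article does not say so in those words. With a panel this small, failure to reject is weak evidence that nothing moved, and it becomes easier to obtain as panellists drop out.

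At stake is the stopping rule. A statement still drifting towards or across 75% may be closed, and so either be left without consensus or accepted on votes that were still moving.

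**Working it through.** The article states no power or detectable shift for these tests, so there is no figure of its own to reproduce.

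**Inputs from the article:** 30–40 panellists, a 7-point scale, two-sided α of 0.05, a 75% consensus line, and a 20% attrition trigger (30 panellists would become 24).

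**Assumptions not in the article:** the within-panellist correlation ρ, the size of the shift, and the starting agreement (a score of 5 or more).

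**Step 1: why ignoring the pairing matters.** The variance of the mean change is 2σ²(1−ρ)/n. An independent-samples test takes it as 2σ²/n. With no shift, its z statistic therefore has standard deviation √(1−ρ), not 1.
- ρ = 0.6: √0.4 = 0.632, so rejection needs |Z| > 1.96/0.632 = 3.10, a probability of about 0.2%.
- ρ = 0.8: √0.2 = 0.447, so rejection needs |Z| > 1.96/0.447 = 4.38, well under 0.1%.

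**Step 2: a shift of 0.4 SD with n = 36.** If 60% agree at the start, agreement after a shift d is Φ(0.253 + d). For d = 0.4 this is Φ(0.653) = 74%. The shift in unpaired standard errors is 0.4/√(2/36) = 1.70.
- Unpaired: the probability is P(Z > (1.96 − 1.70)/√(1−ρ)), about 34% at ρ = 0.6 and 28% at ρ = 0.8.
- Paired: the probability is P(Z > 1.96 − 1.70/√(1−ρ)), about 77% and 97%.

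These are normal approximations. Simulation on a 7-point item (distribution 4/6/10/20/25/20/15%) gives 26–30% for Kruskal-Wallis and 66–89% for signed-rank.

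**Step 3: simulated chance of flagging a shift, n = 30–40.**

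| Shift (SD) | Agreement from 60% to | Kruskal-Wallis, ρ 0.6–0.8 | Wilcoxon signed-rank |
|---|---|---|---|
| 0 | 60% | 0–0.4% | 4–6% |
| 0.2 | 67% | 1–5% | 15–48% |
| 0.3 | 71% | 7–15% | 30–82% |
| 0.4 | 74% | 18–33% | 58–93% |
| 0.5 | 77% | 42–62% | 68–99.8% |
| 0.8 | 85% | 91–99.5% | 97–100% |

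The signed-rank figures use ρ 0.5–0.85 and a start of about 62%, except the 0.4 SD row (ρ 0.6–0.8, start 60%). Over ρ 0.5–0.85 the Kruskal-Wallis figures are 0–0.9%, 1–7%, 4–17%, 39–62% and 89–99.6% at 0, 0.2, 0.3, 0.5 and 0.8 SD. With 24 panellists and 0.5 SD, Kruskal-Wallis flags 27–38% across the correlations tried.

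**Step 4: two-option items.** The independent-samples calculation for 30 to 40 responders per round gives:
- 65% to 75%: 13–16%
- 60% to 75%: 23–30%
- 55% to 75%: 37–47%
- 50% to 75%: 52–64%
- 40% to 75%: 80–90%

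For 80% power at 60% to 75%, n = [1.96√(2·0.675·0.325) + 0.842√(0.24 + 0.1875)]²/0.15² = 152 per round.

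Pairing helps less here. With 5% or 10% of panellists moving against the trend, McNemar flags 60% to 75% in 18–36% (exact) or 26–47% (mid-p) of runs.

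As an example, 21 of 36 rising to 28 of 36 (58% to 78%) crosses the consensus line. The pooled proportion is 49/72 = 0.681, z = 0.194/√(0.681·0.319·2/36) = 1.77, and p = 0.077, so the item is called stable. Exact McNemar depends on the movers: 7 against 0 gives 2/2⁷ = 0.016, but 9 against 2 gives 2(1 + 11 + 55)/2¹¹ = 0.065.

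**The case against.** The strongest reply is that stability does not by itself create consensus. An item must separately reach 75%. Items drawing congruent comments in more than 10% of responses are modified for later rounds, and panellists vet the final statements. These are real but partial safeguards, because none of them measures whether answers have stopped moving.

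It can also be said that consensus is a group proportion, so group-level stability is a defensible target. That stands. It disposes of the worry that panellists who exchange positions go unseen, since an exchange leaves the proportion unchanged. It does not rescue the tests, which also miss movement in the group proportion.

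Three stronger readings are tempting but unsupported:

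- A reader might infer that most real changes of opinion are missed. The article names no relevant shift, and large shifts are usually detected.
- A reader might infer that noisier answers make an item stable sooner. For small or no shifts the reverse holds: with no change Kruskal-Wallis flags about 5% at zero correlation, and almost none at 0.6–0.8.
- A reader might infer that an item which moved once and then settled stays open indefinitely. That would need all rounds pooled in one test, which the article does not state.

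Finally, on two-option and multiple-choice items the main limit is panel size, not pairing. That is correct, and it shapes the remedy.

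**Conclusion.** The point holds for small and moderate shifts. The stated rule applies independent-samples tests to paired answers and takes non-significance as stability. For Likert items with 30–40 panellists and an assumed correlation of 0.6–0.8, it would call stable about 85–99% of shifts of 0.2–0.3 SD and 67–82% of a move from 60% to 74% agreement. Detection is near even at 0.5 SD and about 90% or more at 0.8 SD. On two-option items, rises of up to about 20 points to 75% would be missed more often than not.

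The sizes depend on the assumed correlation, shift and response distribution, and on reading the test as a comparison between rounds. The direction does not depend on the exact values: any positive within-panellist correlation makes the unpaired test conservative, and a non-significant result in a panel of this size cannot show stability.

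**What to change.** Before round 1:

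1. Link each panellist's responses across rounds by a coded ID that keeps panellists anonymous to each other. The article mentions a unique online link but does not say that it identifies individuals across rounds.
2. State that stability compares the two most recent rounds, in panellists who answered both.
3. Declare stability on a prespecified limit. This can be a maximum share of panellists changing option or crossing the agreement cut, or a minimum within-panellist agreement such as weighted kappa. The steering committee sets the value; the article gives no basis for a particular figure.
4. Replace Kruskal-Wallis with Wilcoxon signed-rank for Likert items, and chi-square with McNemar or Stuart-Maxwell for multiple choice. Report these p values as support only, because pairing alone adds little power for binary or multiple-choice items at this panel size.

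The cost is a small procedural change for the linkage, revised wording, and one more round for some statements. The linkage has to be in place from the start, since unlinked anonymous responses cannot be paired afterwards.

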### Consensus process

This study adopts a mixed-methods consensus design to ensure comprehensive stakeholder involvement. Two parallel methodologies will be employed:

Nominal group technique (NGT): to gather and prioritise perspectives from patients and patient care representatives, a structured NGT approach will be used. This technique facilitates in–depth discussion and the ranking of PPCsin a virtually moderated setting. It ensures that diverse lived experiences are reflected and incorporated into the prioritisation process.

Modified Delphi methodology: for consensus among panellists, a modified Delphi process will be undertaken. This will involve multiple anonymous iterative survey rounds, enabling participants to rate and revise their responses based on group feedback.

### Final consensus

The stable statements from Delphi rounds will inform the consensus definition, components, timeframe and appropriate monitoring of PPCs and will be vetted by panellists before publishing.

### Weightage grade

PPCs will be further categorised, ranging from 0–6, with 0 (normal health without disability) to 6 (dead or as bad as being dead).^20^ Panellists will be asked to provide weightage grade for categories 1 to 5 using the WHO Global Burden of Disease Project (WHOGBDP) person trade-off method in the special Delphi rounds for weightage grade.^21^ As a reference framework for this task, the panel members will be provided with the WHOGBDP framework table, clinical vignettes displaying seven disability classes and 22 anchoring example conditions. During the initial Delphi rounds, panellists will also be asked to establish consensus on the relevance and use of the WHOGBDP–based severity grading system for PPCs. The coefficient of variation (CV) will be used to determine the need for additional Delphi rounds, with CV ≤0.5 indicating achievement of substantial consensus.

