### Specific objectives

To generate consensus on the PPCs construct;

To generate consensus on the individual components of PPCs and their definition;

To generate consensus on the timeframe of monitoring for PPCs;

To generate consensus on the methods of monitoring PPCs, and

To generate consensus on the weightage grade of individual PPCs.

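### The CV ≤0.5 consensus rule for weightage grades depends on the mean and on an unstated answer scale, so split panels can be declared in consensus on severe categories

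*Protocol article*

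**What the plan says.** The Introduction makes weightage grading of individual PPCs part of the main objective, and Specific objectives repeats it: "To generate consensus on the weightage grade of individual PPCs".

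Under Weightage grade, the severity classes are bounded at both ends: "PPCs will be further categorised, ranging from 0–6, with 0 (normal health without disability) to 6 (dead or as bad as being dead". Then: "Panellists will be asked to provide weightage grade for categories 1 to 5". The weights are elicited by the "person trade-off method in the special Delphi rounds for weightage grade".

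The decision rule follows: "The coefficient of variation (CV) will be used to determine the need for additional Delphi rounds", "with CV ≤0.5 indicating achievement of substantial consensus". One statistic thus both stops the weighting rounds and declares the result.

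The section gives no reason for 0.5, does not state the numeric scale of the answers, and sets no limit on absolute spread or minimum share in agreement. The 75% agreement threshold and the stability tests under Consensus and stability are specified for Likert and multiple-choice statements only.

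**The concern.** A consensus rule should respond to how far panellists differ. The CV also responds to where on the scale they sit. With the same absolute disagreement, a severe state passes more easily than a mild one.

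The verdict even depends on the direction of scoring. A 0–1 disability weight with mean 0.8 and SD 0.2 has CV 0.2/0.8 = 0.25, which is consensus. The same answers scored as health (mean 0.2, SD 0.2) have CV 1.0, which is not.

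At stake is the meaning of consensus for one of the study's main outputs. A severe category may be closed while panellists are visibly divided. Depending on the scale, a mild one may be sent to further rounds although answers are close in absolute terms.

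**Working it through.** **Inputs.** From Weightage grade: the 0.5 limit, categories 0 to 6, weights sought for categories 1 to 5, person trade-off. Panel size is "An international panel of 35–40 panellists from six continents" in Panellists and "engaging an international multidisciplinary group of 30–40 panellists" in the Abstract; the difference does not change the result. The rule has no sample size or power figure to reproduce. As the answer scale is not stated, three are assumed in turn: 0–1 weights, grades 0–6, grades 1–5.

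**1. Mean above which the rule cannot fail.** On a scale from a to b with mean m, the largest possible SD is √[(m − a)(b − m)], reached with all answers at the two ends.

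- 0–1: largest CV = √[(1 − m)/m]. Setting this ≤0.5 gives (1 − m)/m ≤ 0.25, so m ≥ 0.80. The largest CV is 0.655 at m = 0.7, 0.50 at 0.8 and 0.33 at 0.9.
- 0–6: √[(6 − m)/m] ≤ 0.5 gives m ≥ 4.8.
- 1–5: √[(m − 1)(5 − m)]/m ≤ 0.5 gives 1.25m² − 6m + 5 ≥ 0, with upper root m = 3.73.

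With the n − 1 divisor and 30–40 panellists the bounds rise slightly (0.804–0.805 on 0–1).

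**2. Split panels.**

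- Half at 0.4, half at 1.0: mean 0.7, SD 0.3, CV 0.43. Passes.
- Half at grade 2, half at grade 5: mean 3.5, SD 1.5, CV 0.43. Passes.

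**3. Answers spread evenly over the whole scale.**

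| Scale | Mean | SD | CV | Rule | Random even-chance panels of 30–40 that pass |
|---|---|---|---|---|---|
| Grades 1–5 | 3 | √2 = 1.414 | 0.471 | passes | about 69–72% |
| Grades 0–6 | 3 | 2 | 0.667 | fails | about 2–3% |
| Continuous 0–1 | 0.5 | 1/√12 = 0.289 | 0.577 | fails | about 11–15% |

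The last column is from 100,000 simulated panels per size. For 35 panellists with 7 on each of grades 1–5, the n − 1 SD is √(70/34) = 1.435 and the CV is 0.478: consensus is declared with 20% on any one grade.

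**4. Mild states.**

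- On 0–1 at mean 0.05, the SD may not exceed 0.5 × 0.05 = 0.025. At mean 0.8 it may reach 0.40, which is 16 times as much.
- Thirty-five answers with 12 at 0, 12 at 0.05 and 11 at 0.10 have mean 0.0486, SD 0.0411 and CV 0.85. They fail, although all lie within 0.10 of each other.
- On 1–5 this strictness does not arise. At mean 1.5 the permitted SD is 0.75, and 60%, 30% and 10% on grades 1, 2 and 3 give SD 0.671 and CV 0.45, which passes.

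**The case against.** **The strongest reading fails as a general claim.** A reader might infer that a panel with no agreement meets the rule. Step 3 shows this only if answers are grades 1–5. The categories 1 to 5 in the text may well be the states being weighted and not the answer scale, and on the full 0–6 or 0–1 range an evenly spread panel fails.

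**The two faults do not come from one scale.** Passing an even spread needs 1–5; over-strictness for mild states needs a scale that starts at zero. Only leniency at high means holds on all three. This stands.

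**The bound is a worst case.** Reaching CV 0.5 at a 0–1 mean of 0.8 takes 20% of answers at exactly 0 and 80% at exactly 1. The protocol supplies vignettes, a framework table and 22 anchoring conditions, which make such a vote on a severe category unlikely. That is fair: the documents do not show that real agreement will be absent. But the 0.4/1.0 split is far less extreme and still passes.

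**Severe PPCs dominating a weighted composite.** A reader might infer this. No composite formula is given, and the Discussion leaves open whether weighting is warranted at all, so the point does not rely on it.

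**Relative spread can be defended.** For trade-off weights, 0.05 against 0.10 is a twofold difference, and not everyone would call it trivial. That is a reason to report the CV. It does not justify letting it alone declare consensus at the severe end.

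**Other stopping rules.** Delphi rounds says rounds continue until all statements are stable, but the tests given are for Likert and multiple-choice items. This softens the point only slightly. The answer scale may be stated in a fuller protocol, which would settle which row of step 3 applies but would not remove the dependence on the mean.

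**Conclusion.** The concern holds in this form: CV ≤0.5 depends on the mean and on an answer scale that the article does not state. On each scale considered it is lenient for severe categories and cannot fail above a mean of about 0.80 (0–1), 4.8 (0–6) or 3.73 (1–5). Panels divided into two distant camps can be declared in substantial consensus. Acceptance of a fully even spread is conditional on grades 1–5, and great strictness for mild states is conditional on a scale that starts at zero.

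A reader might go further and conclude that consensus on weights will mean little throughout. The documents do not support that: on a 0–1 scale the rule is demanding for mild states, and nothing shows that panellists will in fact be divided on severe ones. The bounds and split-panel results are exact arithmetic; the choice among the three scales is an assumption. Because this is a stated decision rule on a main objective, it should be changed before the weighting rounds begin.

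**What to change.** 1. State the numeric scale on which panellists give weights, and whether categories 1 to 5 are the states weighted or the permitted answers.
2. Do not let CV ≤0.5 alone declare consensus or end the weighting rounds.
3. Fix, before those rounds, an agreement criterion that does not depend on the mean. For category grades, use the study's own threshold, at least 75% in one category, or an IQR of at most one category. For person trade-off weights, require at least 75% of panellists within a pre-set band around the median.
4. Report the median and IQR for each weight, and keep the CV as descriptive.

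The documents give no band width, so the steering committee must choose one. As an illustration only, take ±0.05. The 0.4/1.0 split fails: with 17 and 18 of 35 panellists in the two camps, at most 18/35 = 51% lie in the band. The mild example at 0, 0.05 and 0.10 passes, as all 35 lie in it. On grades, the even 1–5 spread (20% per grade) and the 2/5 split (about 50% each) both fail the 75% rule. A single absolute band can itself be too generous among mild weights, so its width should be set against the smallest difference between neighbouring categories that the committee wants to distinguish.

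The change to the text is short. The practical cost is that some severe-category weights may need a further round, in a study that already allows for attrition above 20%, or may have to be reported as not reaching consensus. Changing the rule after the answers are in would mean choosing a threshold with the results in view.
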